### Program facilitators

Community leaders of the respective intervention villages will propose one eligible candidate of each gender from the local village to act as facilitators of the program. To be considered eligible the potential facilitator must: have completed secondary education, be fluent in English, be respected in the village, be a non-smoker, and have an interest in health and desire to positively impact the health of their village. ADRA Australia will provide the local village facilitators with two weeks of training using Strength Based [26–28] and Appreciative Inquiry (AI) approaches. The training sessions will cover the principles of the CHIP intervention and the REFLECT methodology, as well as the development of facilitation skills and the research methods used in the study.

Following the training, the local ADRA supervisor together with the facilitators from the study villages will collaborate with ADRA Australia and the local ADRA office to ensure a Facilitators Manual (including 18 lesson plans) meet the local context. Following the 6-month program, this collaborative process will be repeated to further contextualise the Facilitator Training and Process Manual’s for the Pacific. The local ADRA supervisor will be responsible for follow up, mentoring the village facilitator and monitoring the program and research.

### Intervention

Participants will receive 6 months of the contextualised 18 session ‘Live More’ program which is based on and follows the order of the 18 session ‘Westernised’ CHIP intervention, which has been previously described [19]. Themes covered include: the causes of NCDs; the benefits of positive lifestyle choices, particularly diet and physical activity as therapy for conditions including obesity, type 2 diabetes, and CVD; and positive psychology and how this influences long-term health habits, as well as stress management, forgiveness, and self-worth.

Participants will meet three times a week in the first month, then once a week for the next two months, followed by once a month for the next three months. The specific content of the ‘Live More’ sessions is outlined in Table 1.

**Table 1 Tab1:** Time line and specific content of the 'Live More' program

Week	Session
0	Baseline biometric measurement, completion of lifestyle questionnaire and demographics
1	1. ‘The Rise and Rise of Chronic Disease’. 2. ‘Lifestyle is the Best Medicine’. 3. ‘The Common Denominator of Chronic Disease’.
2	4. ‘The Optimal Lifestyle’. 5. ‘Eat More, Weigh Less’. 6. ‘Fiber, Your New Best Friend’.
3	7. ‘Disarming Diabetes’. 8. ‘The Heart of the Matter – Heart Health’. 9. ‘Controlling blood pressure and discovering protein’.
4	10. ‘Bone Health Essentials’. 11. ‘Cancer Prevention’. 12. ‘How to grow a family garden. What to grow and when?’
5	30-day biometric measurement, completion of lifestyle questionnaire and feedback. Discussion on understanding results and taking action (with health professional), followed by ‘Circle’ feast/celebration (meal preparation using ‘Live More’ principles learned in earlier sessions).
6	13. ‘Become what you believe and your DNA is not your destiny’.
7	14. ‘Practicing forgiveness’.
8	15. ‘Re-engineering your environment’.
9	16. ‘Stress-relieving strategies’.
10	17. ‘Fix how you feel’.
11	18. ‘From Surviving to Thriving’
12	3-month biometric measurement, completion of lifestyle questionnaire and feedback.
24	3-month biometric measurement, completion of lifestyle questionnaire and feedback.

Each session will typically involve meeting in the ‘Reflect Circle’ where all participants have the opportunity to participate. The session will commence with the facilitator welcoming the participants in a culturally appropriate way and ensuring no-one feels excluded. Participants will be encouraged to discuss their progress and ask any questions that have arisen since the previous session. Using the lesson plan, the predetermined participatory technique and the necessary aids, the facilitator will introduce the theme for the session by exploring what the participants already know about themselves and their local situation. In particular, graphics/visuals in the form of maps, pictures, calendars and matrices will be utilised to describe their current situation and understandings. Following this activity, the participants will be further drawn into the session’s topic by use of a trigger picture, where they will be asked to describe what they see. Throughout this discussion, information will be shared with the group to enhance their understanding of the topic. When all material included in the lesson plan is covered, the facilitator will guide the participants into an action plan to incorporate the learnings from that session into their lives (e.g. how to incorporate 10,000 steps into their day). The session will conclude with congratulations for success so far in the health journey and a reminder of the time and venue for the next session. This whole process empowers the participants to openly discuss their situation and develop strategies to address the issue introduced in that session.

At the end of the 6-months, there will be another biometric measurement, completion of the lifestyle questionnaire and personal feedback. A group feedback session will follow where the achievements of the groups will be acknowledged and graduation certificates distributed. The celebrations will culminate with a ‘Live more’ friendly feast.

### Control villages

In each of the control villages printed health education material developed by the local Ministry of Health will be presented at the first health screening. At each subsequent assessment point, the HP will invite the participant to ask any health related questions from the health literature that was provided at baseline.

### Outcome measures

Data on biometrics, blood measures and health behaviour will be collected on individuals in the intervention and control villages at program entry (baseline), one month, three months and six months by a team of HP’s. A medical assessment, including personal and family health history will be collected at program entry only. The following measurements will be collected:Height, weight, body mass index (BMI), waist circumference and blood pressure will be measured on site by a HP. Weight (in light clothing with shoes removed), to determine BMI, will be measured by a HP, following 12 h fast using commercial weight scales. Blood pressure will be measured using a medical sphygmomanometer by a HP. Measurements will be repeated at each time point using the same equipment to reduce systematic measurement error.Fasting lipid profile and plasma glucose will be drawn on site. Whole blood samples will be collected into capillary and heparinised tubes by the designated HP following via finger prick method. Samples will be removed from the tube for analysis, using the CardioChek PA portable blood analyser within 5 min of the blood draw. All alcohol swabs, lancets, used blood tubes and CardioChek pads will be deposited in biohazard material bags and taken by the HP to the local pathology laboratory or public hospital for incineration.Physical activity will be quantified using a pedometer supplied to the participants who will record their daily steps taken in a log book provided. For illiterate participants, the final reading at the end of each day will be recorded by someone with literacy skills from the same village.Health related behaviours will be assessed using a lifestyle questionnaire administered verbally by the HP (requirement due to the relatively low levels of literacy of the participants). A medical doctor or nurse will be present at the beginning of the project to collect and record information in private. The information will then be given to the ADRA supervisor who will keep it in a locked file.Lifestyle habits include: smoking, alcohol, kava and betel nut usage; frequency of daily consumption of limited key foods including, fruit and vegetables, fatty and processed foods, meat and wholegrains/cereals; frequency of weekly light, moderate and strenuous physical activitySubjective wellbeing include: emotional health, supportive relationshipMedical history, including personal and family history of heart problems, high blood pressure and blood glucose, cancer and breathing problems.Medication usage. During the initial medical assessment, the participants will present all medications they are taking and the type and dosage will be recorded by the HP.

### Process evaluation

Unlike ‘Outcome evaluation’, as outlined above, which assesses the effectiveness of the program to impact the health of the participants, ‘Process Evaluation’ gives an understanding of *how* the outcome was achieved.

Process data regarding program operations, implementation and delivery will be collected to complement the outcome data. Process measures will include:Participant attendance at sessions. Participants will be deemed to have completed the program if they attend 75 % of the sessions (i.e. 14 of the 18 ‘Live More’ sessions);Facilitator self-efficacy and competency survey. The facilitators will respond to a range of likert items relating to their perceived: level of skill and confidence in program delivery, interest in health before and after their training, and impact on the health of the participants. The facilitators will also be asked in a semi-structured interview about factors enabling their continued engagement and strategies used to engage group participation and attendance;Participant focus group discussion. A minimum of 5 participants from each village will be asked to relay their most significant change during the program. Most Significant Change Stories (MSC) methodology [29] will be used to tease out the participants’ perceived change and benefits from the program;Participant satisfaction with all components of the intervention will be assessed by semi-structured interview to inform the future development of the intervention.

### Statistical methods

The (biomedical) data will be analysed using IBM™ Statistics (version 21). Continuous data will be expressed as number, mean, standard deviation (SD). Categorical data will be summarized as counts and percentages. For each country, differences between participants in the intervention and control groups at baseline will be examined using Chi square for categorical variables and independent samples t-tests for continuous variables. The extent of changes (percent, and mean with 95 % confidence intervals (CI)) from baseline, one month, three months and six months will be assessed using Analysis of Variance (repeated measures). For all analyses, results are considered significant at *P* < 0.05.

The qualitative data obtained through the various participatory, qualitative techniques listed above, will first be checked for accuracy with some of the participants and then with program staff (facilitators and supervisor). For the analysis, focus group data from the first village will be broken down into parts and examined for emergent categories (themes or patterns) and sub-categories, then coded. These categories and sub-categories may at this stage start to show a theory. Coding of the second focus groups will be done with the first in mind. Subsequent focus group discussion in the other two countries will also be coded with the emerging theory in mind.

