### Village eligibility criteria and randomisation

A village will be eligible to participate in the study if there is:an expressed endorsement and positive commitment by the village chief/community leader;observable overweight in the community (estimation of at least 40 % as observed by the ADRA Supervisor);relatively low literacy rate/education level in the potential participants as indicated by the community leader;adequate interest by residents who meet the participant eligibility criteria (described below) to achieve the required cluster sample size (described below);willingness to participate in the study as either a treatment or control site.

Once eligible villages are identified, ensuring they are not in immediate proximity to each other to avoid cluster contamination, the villages in each country will be randomised to either intervention or control by a researcher not familiar with the geographic location or nature of the village. Figure 1 shows the sequence for allocation of sites to treatment and control conditions.

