### Power calculation

Data from CHIP interventions conducted in Australia and New Zealand [20] were used for the power analyses. Power calculations were conducted on all the biometrics to be measured in the present study, which indicated that of all the biometrics, detecting a significant change in triglycerides would require the greatest sample size. Using an estimated mean baseline triglyceride level of 1.15 mmol/L with a standard deviation of 0.33 mmol/L, to achieve a 5 % level of significance with 80 % power will require 87 participants in each of the three countries. Allowing for a 10 % loss to follow up at 6 months, in each country a total of 96 participants will be recruited, constituting two intervention villages each with 24 participants and two control villages each with 24 participants. In total, 288 participants from the three countries will be involved in the study: 144 intervention and 144 control.

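### Testing the arms for baseline differences country by country at P < 0.05 is a poor guide to imbalance, and the tests ignore that villages were allocated

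*Protocol article*

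**What the plan says.** The Statistical methods section of the protocol article sets out the baseline comparison, to be made separately by country, in one sentence, which says that "differences between participants in the intervention and control groups at baseline will be examined using Chi square for categorical variables and independent samples t-tests", with the t-tests applied to the continuous measures. The comparison is between participants, and village does not enter it. The same paragraph closes with a general rule, "For all analyses, results are considered significant at *P* < 0.05", which covers the baseline tests as well.

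The unit of allocation is the village. Under Village eligibility criteria and randomisation, "the villages in each country will be randomised to either intervention or control". The Power calculation section gives the numbers per country: "two intervention villages each with 24 participants and two control villages each with 24 participants".

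The article does not say what will follow from a significant or a non-significant baseline result.

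**The concern.** Two features of these tests make them unsuited to judging imbalance.

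First, whether an imbalance matters depends on its size and on how strongly the variable predicts the outcome. A P value measures neither. A small difference in a variable of no prognostic weight can be flagged, while a sizeable one in a strong predictor can pass.

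Second, the tests take 48 and 48 independent participants as their basis, although only two villages per arm were allocated in each country. If people in one village resemble each other, the standard error is too small and chance differences between villages are flagged more often than 5% of the time.

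The stake is the reading of the baseline table. Flags could be taken as meaningful differences, or their absence as reassurance, when the tests support neither.

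**Working it through.** **Inputs from the article**
- Two villages against two per country, 24 participants each: 2 × 24 = 48 per arm, 96 per country, 288 over three countries, as stated.
- Significance level 0.05. Sidedness is not stated; two-sided is assumed.
- Triglycerides: mean 1.15 mmol/L, SD 0.33 mmol/L (Power calculation).

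The article gives no error rate for the baseline tests, so there is no figure of its own to reproduce. Its sample size is not in question here.

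**Assumptions**
- Nine continuous baseline biometrics: BMI, waist, systolic and diastolic pressure, four lipids and glucose. This gives 9 × 3 = 27 tests. The categorical variables would add more.
- ICC of 0, 0.01, 0.05 or 0.10. The article gives none.

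**Step 1. Chance flags with no village correlation**

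Expected number = 27 × 0.05 = 1.35, about 1.4. If the tests were independent, the chance of at least one flag would be 1 − 0.95^27 = 75%. The biometrics are correlated, so this is indicative only. With 5 to 30 variables per country, the expected number runs from 15 × 0.05 = 0.75 to 90 × 0.05 = 4.5.

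**Step 2. Chance flags when village is ignored**

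The design effect for villages of 24 is DE = 1 + 23 × ICC. The approximate rejection rate is 2 × [1 − Φ(1.9855/√DE)], where 1.9855 is the t critical value on 94 degrees of freedom. Null data for two against two villages of 24 were also simulated twice (40,000 and 20,000 data sets) and analysed with the participant-level t-test.

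| Assumed ICC | DE | Approximate rate | Simulated rate (two runs) | Expected flags in 27 tests (simulated) |
|---|---|---|---|---|
| 0 | 1.00 | 4.7% | 5.0%, 5.1% | 1.4 |
| 0.01 | 1.23 | 7.3% | 7.7%, 8.2% | 2.1 to 2.2 |
| 0.05 | 2.15 | 17.6% | 18.5%, 18.1% | 4.9 to 5.0 |
| 0.10 | 3.30 | 27.4% | 29.0%, 28.9% | 7.8 |

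Under clustering the simulated rates sit slightly above the approximation because the pooled SD captures only part of the between-village variance. Everything above the first row is due to ignoring village. Baseline testing as such accounts for the 1.4.

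**Step 3. What a non-significant result can show**

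With 48 per arm and no clustering, the standard error of a difference in SD units is √(2/48) = 0.204.
- Smallest observed difference reaching P < 0.05: 1.9855 × 0.204 = 0.41 SD. For triglycerides this is 0.405 × 0.33 = 0.13 mmol/L, or 0.134/1.15 = 12% of the stated mean. Any smaller observed difference passes unflagged.
- Power for an underlying difference of 0.3 SD: the noncentrality is 0.3/0.204 = 1.47, and the two-sided t-test has 31% power.
- Power for 0.5 SD: 68%.

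**The case against.** The strongest reply is that nothing harmful is written down. The article says only that baseline differences will be examined. A reader might infer that non-significance will be taken as balance, or that adjustment variables will be picked by baseline P value. The article states neither, so both remain possible misuses and not features of the plan. That part of the reply stands.

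A second reply is that baseline differences here need not be pure chance. Villages are randomised, but participants volunteer at a village meeting and must be ready to take part in the intervention. The article does not say outright whether this happens before or after allocation. If after, the arms could differ through differential volunteering, and looking at comparability has a real purpose. This also stands, so it would be too strong to call every flagged difference chance. It does not rescue the tests: with two villages per arm, a participant-level test cannot separate differential volunteering from chance variation between villages.

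A third reply is that the larger counts reflect a unit-of-analysis fault and not baseline testing itself. That is correct, and the table keeps the two apart. A cluster-corrected test would repair the error rate but would still say nothing about the size or prognostic weight of an imbalance.

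Finally, a list of prognostic covariates may properly sit in an analysis plan that is not shown. Its absence from the article is not a fault and is not raised here.

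**Conclusion.** The point holds as a minor one. The article prescribes a stated analysis that suits its purpose poorly and is carried out on the wrong unit. Under the assumption of 27 tests, about 1.4 chance flags are expected with no village correlation, and about 2, 5 or 8 at ICCs of 0.01, 0.05 or 0.10. Non-significance is weak evidence of comparability: even without clustering, an underlying 0.3 SD difference is missed about 69% of the time (100% − 31%).

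The counts depend on the assumed number of variables and ICCs. The 0.41 SD threshold and the power figures depend only on 48 against 48 participants, a two-sided 5% test and independent observations.

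A reader might go further and conclude that the outcome comparison is biased. The document does not support that. The tests would affect the outcome results only if they drove covariate choice or interpretation, and the article does not say that they will.

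**What to change.** - Delete the baseline chi-square and t-tests from Statistical methods.
- Report baseline mean (SD) or count (%) by arm and by village, without P values. Village-level values let a reader see an imbalance whether it arose by chance or through who volunteered.
- State that the between-arm analysis of each outcome adjusts for the baseline value of that outcome, whatever imbalance is observed.

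The cost is a rewording of the baseline sentence, one added sentence on adjustment and a differently laid out baseline table. The summaries are already planned and the baseline values already collected, so neither data collection nor sample size changes.

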## Methods/Design

### Study design

The ’Live More’ program will be evaluated using a cluster randomised controlled trial. The study design is illustrated in Fig. 1. The 6-month intervention will be conducted in three Pacific Island countries: Solomon Islands, Vanuatu and Fiji. In each country there will be two intervention villages and two control, resulting in a total of six intervention villages and six control villages across the three countries. Assessments will be conducted at baseline, and repeated at 30 days, 3 months and 6 months post baseline. The design, conduct and reporting of this study will adhere to the Consolidated Standards of Reporting Trials (CONSORT) guidelines for group trials.

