### Participant recruitment and eligibility criteria

Participants will be recruited through a village meeting called by the village elder. During this meeting, an ADRA Supervisor together with a designated health professional (HP-doctor or nurse) will provide information about the program. Following the information session, a call for volunteers who meet the eligibility criteria will be made. To be considered eligible to participate in the study the individuals will:be 18 years of age or older;live permanently in the village (for the duration of the program)have a waist circumference of ≥92 cm for men and ≥80 cm for women (as levels at and above these are indicative of risk of NCD) [25];be prepared to engage in the ‘Live More’ intervention and monthly post-program meetings (total duration of 6 months);be able to provide their own meals (because this will enable compliance with the program’s dietary recommendations).

An equal number of males and females will be recruited for the study. No payments will be requested of participants and the participants will not receive any financial remuneration for their involvement.

Individuals will be considered ineligible to participate in the study if they meet one or more of the following exclusion criteria:unstable angina;myocardial infarction within the previous 12 months;coronary by-pass surgery within the previous 12 months;other medical contraindications for dietary change or increased physical activity, as determined by the HP;chronic infectious disease/s, as participants illness may affect participation in the program;are a direct relative of the village chief (to reduce bias in recruiting).

All eligible participants will be explained the consent process, and informed that all personal information will be confidential and anonymous. They will then be asked to sign or make their mark on the consent form or give the appointed HP for the study verbal consent to sign on their behalf in the presence of a witness (in case of literacy constraints).

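### The outcome analysis is stated as change from baseline; no between-arm contrast at follow-up and no baseline adjustment is named

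*Protocol article*

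**What the plan says.** The Statistical methods section of the protocol article names two inferential procedures for the quantitative data.

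- For baseline: "For each country, differences between participants in the intervention and control groups at baseline will be examined". Categorical variables get a chi-square test and continuous ones a two-sample t-test.
- For outcomes, the quantities reported are the percent change and the mean change, the latter with its 95% CI. The article gives the visits and the method in these words: "from baseline, one month, three months and six months will be assessed using Analysis of Variance (repeated measures").

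The first names the two arms. The second does not: it mentions no group factor, group-by-time term, difference between arms at any follow-up visit, or baseline covariate. The confidence interval is attached to the change. A 5% significance level applies to all analyses.

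The Study design section says that the "program will be evaluated using a cluster randomised controlled trial". The Power calculation section again speaks of change, saying that "detecting a significant change in triglycerides would require the greatest sample size".

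**The concern.** The effect of a programme in a randomised trial is the difference between intervention and control. The outcome sentence, read as it stands, asks whether participants changed over time, and the comparison of arms is confined to baseline.

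Both arms could change without any programme effect:

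- Participants must "have a waist circumference of" at least a fixed cut-off, so some fall back towards the mean is expected, mainly in waist and its correlates.
- Both arms are measured on four occasions over six months, so repeated screening and season act on both.
- Control participants also receive printed health material and are invited to put questions to a health professional at each later visit.

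A test of change, pooled over arms or made within each arm, does not separate these influences from the programme. The lesser issue is precision: the participant's own baseline value is collected, but the plan does not say that it will be used as a covariate.

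**Working it through.** **1. The plan's own figure.** The Power calculation section gives 87 evaluable participants per country for triglycerides (SD 0.33 mmol/L, 5% significance, 80% power). No effect size is stated, so 87 cannot be reproduced directly. Solving backwards, two-sided, with 1.960 + 0.842 = 2.802:

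- as a comparison of two arms of 43.5: 2.802 × 0.33 × √(2/43.5) = 0.198 mmol/L, which is 17% of the baseline mean of 1.15;
- as a one-sample change in 87 people, if 0.33 is the SD of change: 2.802 × 0.33/√87 = 0.099 mmol/L, which is 8.6%.

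The article does not say which was meant, so the sample size does not settle which contrast the analysis targets.

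**2. What a group-by-time term would give.** Two arms and four time points give (2 − 1) × (4 − 1) = 3 degrees of freedom. That term is a between-arm comparison, but it tests for any difference in profile. It gives no estimate with a CI at a chosen visit, and baseline enters as one of the outcomes.

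**3. What judging by separate within-arm tests would give.** Suppose that the true change is equal in both arms and each within-arm test has power p. Treating the arms as independent, the probability that only the intervention arm is significant is p(1 − p):

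- p = 0.5: 0.5 × 0.5 = 0.25;
- p = 0.8: 0.8 × 0.2 = 0.16.

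A simulation illustrates this: 4,000 trials per row, 43 per arm, SD 0.33, two time points, assumed baseline-to-follow-up correlation r = 0.6, no clustering, no treatment effect.

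| Common fall in both arms (mmol/L) | Pooled test of time significant | One arm significant, the other not (either way round) | Between-arm test of change significant |
|---|---|---|---|
| 0.05 | 34% | 31% | 5% |
| 0.10 | 87% | 50% | 5% |
| 0.15 | 100% | 19% | 5% |

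Only the between-arm test keeps its 5% error rate as a test of the programme.

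**4. Baseline adjustment.** With outcome variance σ² at both visits and correlation r, the individual-level variance is 2σ²(1 − r) for a change score and σ²(1 − r²) after adjustment. The ratio is (1 − r²)/(2(1 − r)) = (1 + r)/2:

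- r = 0.5: 0.75/1.00 = 0.75;
- r = 0.6: 0.64/0.80 = 0.80;
- r = 0.7: 0.51/0.60 = 0.85.

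The article gives no value of r; these are assumptions.

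**The case against.** The strongest defence is that the text is silent rather than wrong. Repeated-measures ANOVA routinely takes a between-subject group factor, and its group-by-time term is a randomised comparison of change. The article describes a cluster randomised trial, promises to follow CONSORT for group trials, and collects outcomes in both arms at every visit. Nothing says that arms will be pooled or analysed separately. A condensed article also commonly leaves model terms and covariates to an analysis plan.

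Much of this stands, and it rules out several stronger readings that a reader might infer:

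- *That the trial will be analysed as a before-after study.* The text does not say so; the authors may have intended the group-by-time term.
- *That the trial was powered for a before-after change.* The wording allows it, but the missing effect size leaves both readings open.
- *That success will be declared when only the intervention arm changes significantly.* No such rule is stated, so the 25-16% is conditional on a rule from outside the plan.
- *That everyone receives the health literature.* The Control villages section provides it to control villages; nothing says that intervention participants receive it.
- *That baseline adjustment is worth a third more participants here (1/0.75 = 1.33).* That figure needs r = 0.5 and ignores villages. Omitting the covariate costs precision but does not bias a randomised comparison on average.

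What the defence does not remove is that the article does state its outcome analysis. It specifies a between-arm comparison for baseline and none for follow-up, and the Power calculation section repeats the language of change. The most favourable reading still gives no between-arm estimate at a stated visit.

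**Conclusion.** The point holds for the plan as written. The randomised contrast is not named, and the estimate that readers will want (intervention minus control, with CI, at a stated visit) does not follow from the analysis described. This is the main defect; the absence of baseline adjustment is secondary.

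The size depends on what is done in practice. If a group-by-time term is fitted, the loss is an interpretable estimate and some precision. If only change over time is tested, a shared fall could be taken for a programme effect: in the simulation, a common fall of 0.10 mmol/L made the pooled test significant in 87% of trials with no effect. The simulation rests on r = 0.6 and no clustering, and the article documents no common change of any size. The variance ratio of 0.75-0.85 assumes r of 0.5-0.7 and covers the individual level only; the gain is smaller where between-village variance dominates.

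**What to change.** In the Statistical methods section:

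- State the main analysis of each biometric as the intervention-minus-control difference at 6 months with its 95% CI, adjusted for the participant's own baseline value and for country (villages are randomised within country), in an analysis that accounts for village.
- Give the same contrast at 30 days and 3 months as secondary.
- Report within-arm and percent changes as descriptive only.

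The article names no primary time point. Six months is a natural choice because the programme ends then and the allowance for loss to follow-up refers to it. Adjusting for sex and dropping the baseline significance tests are optional.

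No new data are needed, since every variable is already collected. The cost is analysis work, including a method that remains valid with only 12 villages.
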